
### Sample size estimation

#### QST sensory profiles

Published sample size guidelines for QST clustering in peripheral nerve injury^75^ suggest that for strong effects (effect size=0.7) a sample size of <180 patients will produce a subpopulation with thermal and mechanical hyperalgesia large enough to conduct a study with 80% power, at an alpha 0.05. To calculate QST z-scores, at least eight controls are required for each area and age decade.^76^ Our feasibility study included patients of 7 age decades with three main pain areas. We will, therefore, need n=168 controls.

#### K-means and hierarchical clustering after PCA

Using the two first principal dimensions for three variable domains (self-reported profiling, QST, inflammatory markers), we will need 2^6^=64 patients to perform k-means clustering with adequate power.^77^

#### Algorithmic cluster analysis

Assuming k=4 clusters, we will be able to identify moderate effects (effect size=0.25) with an one-way analysis of variance between four groups at an alpha level of 0.05, 80% power.

#### Predictor profiling

FORECAST aims to identify prognostic factors (the first step in the PROGRESS framework)^78^ rather than developing a clinical prognostic tool or individual risk model which requires much larger sample sizes. We will use robust algorithms that include feature selection, and we will assess model performance using methods developed for small data sets and robust metrics. As this part is an exploratory analysis that could shape future hypotheses and validation studies, our sample size is adequate. Given the anticipated sample size ratios with chronic (180×30%=54) and resolved sciatica (180×70%=126) and accounting for 15% attrition (see feasibility study), we will be able to identify moderate effects (effect size=0.5) using a two-tailed Wilcoxon-Mann-Whitney test (power 81%, alpha 0.05).

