## Introduction

Low back pain (LBP) is associated with more disability than any other condition.^1^ Up to 60% of patients with LBP also experience leg pain, which is associated with worse health outcomes. In some cases, the leg pain is caused by nerve root involvement, commonly referred to as ‘sciatica,’ whereas some patients with ‘sciatica’ have pain of predominantly nociceptive character, others develop neuropathic (nerve related) pain, which is characterised by burning pain, electric shocks or tingling. The presence of neuropathic pain in sciatica further increases suffering and disability.^2^ The management of sciatica is, therefore, a priority. The National Institute for Health and Care Excellence (NICE) guidelines recommend a period of non-invasive treatment (eg, medication, physiotherapy) before invasive treatment (eg, surgery) is considered.^3^ Sadly, first-line management for patients with sciatica remains largely ineffective^4 5^ and at least one-third develops persistent pain and disability lasting a year or longer.^6–10^

It remains unclear why some patients develop persistent sciatica. Two recent systematic reviews have established that none of the traditionally considered clinical parameters (eg, pain intensity, routine MRI, mental well-being) are consistent prognostic factors.^11 12^ Since those publications, the largest prognostic study in patients with sciatica in primary care^8^ identified several factors that are weakly associated with improvement, these included shorter pain duration, belief that symptoms will not last long, myotomal weakness, overall impact of sciatica. However, at 12 months, only two factors were independently associated with outcome in the multivariable model analysis. This restricts the usefulness of predictive modelling for risk estimation of outcome for individual patients. The absence of prognostic factors hinders the early identification of patients at risk of developing persistent pain and prevents personalised treatments.

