### Participants

We will include n=180 patients with acute/subacute ‘sciatica’ and n=168 healthy age and gender-matched participants without symptoms of sciatica/LBP. Healthy participants are important to establish normative values for blood markers, somatosensory profiling and neuroimaging.

People aged >18 years with a clinical diagnosis of ‘sciatica’ will be recruited from primary care in Oxfordshire (eg, primary care providers for the National Health Service as wellGeneral Practitioners, Physiotherapy, Osteopathy and Chiropractor clinics) and through leaflets on public noticeboards. Sciatica symptom onset of the current episode needs to be within the past 3 months with a symptom-free period of at least 3 months preceding the current sciatica symptoms. The inclusion criteria for patients with ‘sciatica’ are based on a published diagnostic model,^19^ which includes five weighted parameters (self-reported sensory changes, below knee pain, leg pain worse than back pain, neurodynamic tests and neurological deficit). A sum score >4 will be defined as sciatica, with a mean predicted probability of 83%. In addition, patients with suspected sciatica will undergo a clinical examination by a physiotherapist to further confirm the diagnosis of sciatica and rule out other diagnoses (see the section additional phenotypic data below).

The following exclusion criteria will apply; presence of other nerve-related disorders (eg, diabetic neuropathy, stroke), previous lumbar spine surgery, serious spinal diseases (eg, infection, cauda equina syndrome, metastatic lesions), chronic inflammatory disorders, other pain conditions that may confound assessment (eg, fibromyalgia), pregnancy, insufficient command of the English language to obtain consent/complete questionnaires and contraindications to MRI for those selected for scanning.

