### Outcome measures to define pain persistence

The final selection of our outcome measures has been guided by our PAG and feedback from participants in the feasibility study. Pain persistence will be defined with the sciatica bothersomeness index (SBI)^21^ and a Numerical Pain Rating Scale (0 no pain to 10 worst pain imaginable, primary outcomes). The Sciatica Bothersomeness Index (SBI) includes elements of leg pain as well as sensory and motor disturbances, thus providing a comprehensive measure of different sciatica symptoms. This index has shown good discrimination between self-reported successful and non-successful outcome in patients with sciatica^22^ and has been favoured by our PAG. In our feasibility study both outcome measures identified 38% of participants who developed persistent pain, which is in line with previous reports.^9^ In line with recommendations, we will use continuous outcomes for statistical analyses. We may use dichotomisation to help data presentation in figures/tables. In this case, we will use a cut-off of>6.5 on the SBI, which has good validity to identify patients with unsuccessful sciatica outcome.^22^

We may also run analyses using secondary outcomes (eg, disability using Oswestry Disability Index (ODI 2.1a),^23^ self-perceived change using Global Rating of Change Scale.^24^

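### The stated 81% Wilcoxon-Mann-Whitney power is not reproduced after 15% attrition under the usual assumptions: about 79% with normal data, 74% at minimum efficiency (minor)

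*Protocol article*

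**What the plan says.** The relevant text is in the protocol article, Sample size estimation, Predictor profiling.

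- **Group sizes.** The anticipated split is "chronic (180×30%=54) and resolved sciatica (180×70%=126"), that is 30% and 70% of the 180 patients. The Participants section fixes that total: "We will include n=180 patients with acute/subacute" sciatica. Attrition therefore comes off 180; it has not already been added to it.
- **Attrition.** The sentence continues "accounting for 15% attrition (see feasibility study").
- **Claim.** "we will be able to identify moderate effects (effect size=0.5"), "using a two-tailed Wilcoxon-Mann-Whitney test (power 81%, alpha 0.05").

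The paragraph gives neither the group sizes after attrition nor the distribution or efficiency assumed for the Wilcoxon test.

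Two other places bear on the persistence rate. The Introduction says that "at least one-third develops persistent pain and disability lasting a year or longer". Under Outcome measures to define pain persistence, the feasibility study is reported thus: "both outcome measures identified 38% of participants who developed persistent pain".

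**The concern.** The sentence supplies every input to a power calculation except the parent distribution, so a reader can try to repeat it. With the losses deducted, the named test falls short of 81% under both settings most often used for it, the normal parent and the minimum-efficiency bound. On each it also falls below the conventional 80%.

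This is the only power figure given for the predictor aim, one of the study's two aims. If 81% is really the value before losses, the sentence credits the design with an allowance for attrition that was not made. The like-for-like figure would then be 74%, an overstatement of 6.6 points.

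**Working it through.** **Inputs (Predictor profiling).** n = 54 and 126; attrition 15%; effect size d = 0.5, read as a standardised mean difference (assumption); two-sided alpha 0.05; stated power 81%.

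**Groups after attrition.** 54 × 0.85 = 45.9 and 126 × 0.85 = 107.1, so 46 v 107 (total 153).

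**Method.** Multiply each group size by the asymptotic relative efficiency (ARE) of the Wilcoxon test against the t test, then use the noncentral t distribution:

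- noncentrality δ = d × √(ARE × n₁n₂/(n₁+n₂))
- degrees of freedom = ARE × (n₁+n₂) − 2
- power = P(|t(δ)| > critical value)

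The ARE is 3/π = 0.955 for a normal parent, π²/9 = 1.097 for a logistic parent, and 0.864 at its minimum over all parents.

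**Step 1: where 81% comes from.** Two routes reach it while keeping the stated 30:70 split.

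- *Full 54 v 126, minimum ARE.* n₁n₂/(n₁+n₂) = 6804/180 = 37.8. δ = 0.5 × √(0.864 × 37.8) = 2.857. Power = **81.0%**. Attrition is not deducted.
- *46 v 107, comparison of two means by normal approximation.* n₁n₂/(n₁+n₂) = 4922/153 = 32.17. δ = 0.5 × √32.17 = 2.836. Power = Φ(2.836 − 1.960) = Φ(0.876) = **80.9%**. Attrition is deducted, but there is no Wilcoxon efficiency loss.

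A third route, one-third persistence (51 v 102 after attrition, normal data), gives 80.8% but contradicts the stated 30%.

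**Step 2: the calculation as described, Wilcoxon at 46 v 107.**

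| Parent or setting | ARE | δ | Power |
|---|---|---|---|
| Minimum efficiency | 0.864 | 2.636 | 74.4% |
| Normal | 0.955 | 2.771 | 78.6% |
| ARE = 1 (same as the t test) | 1.000 | 2.836 | 80.5% |
| Logistic | 1.097 | 2.970 | 84.0% |

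Direct simulation of the Wilcoxon test with normal data (40,000 runs, 46 v 107) gives 78.5%, or 78.4% with continuity correction, in agreement with the normal row.

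**Step 3: size of the gap.** Normal data: 81.0 − 78.6 = 2.4 points. Minimum efficiency: 81.0 − 74.4 = 6.6 points. The effect detectable with 80% power at 46 v 107 is 0.51 with normal data and 0.54 at minimum efficiency.

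**Step 4: what would make 81% right.** For power to round to 81% at 46 v 107, the ARE must lie between about 1.001 and 1.027; an ARE of 1.014 gives exactly 81.0%. This is a narrow band, but mildly heavy-tailed parents come close: simulated power is about 80 to 81% for a t parent with 15 degrees of freedom and about 82% with 10.

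**Step 5: sensitivity to the persistence rate.** With 38% persistence, 153 × 0.38 = 58 and 153 − 58 = 95. Power is 83.0% with normal data and 79.1% at minimum efficiency.

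**The case against.** The strongest objection is that Wilcoxon power depends on a parent distribution that the article does not name. The normal (78.6%) and logistic (84.0%) values bracket 81%, and a parent only slightly heavier-tailed than the normal would deliver it. This stands: it cannot be said without qualification that the design fails to give 81%. What can be said is that neither the normal parent nor the minimum-efficiency bound gives it after attrition, and that nothing in the article points to a parent in the narrow band that does.

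A reader might infer that attrition was simply forgotten, because 54 v 126 at minimum efficiency matches so closely. The article does not establish this. The two-mean approximation at 46 v 107 matches equally well after rounding, and on that route attrition was deducted as stated.

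A reader might also infer that the sample size loses its justification. The paragraph does not support that either. It rests adequacy on the exploratory purpose of this part and disclaims building a prognostic tool; the power sentence follows as an illustration. The article also plans to analyse continuous outcomes, with dichotomisation mainly for presentation, so the two-group Wilcoxon comparison is a benchmark and not the main prognostic analysis.

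Finally, a condensed article may leave distributional assumptions to a fuller document. Their absence alone would not be a finding. The point is that the printed figure does not follow from the printed inputs under the usual assumptions.

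**Conclusion.** The point holds, as a minor one. On the article's own inputs, the two-tailed Wilcoxon-Mann-Whitney test has about 79% power with normal data and 74% at minimum efficiency, not 81%. This rests on three assumptions: effect size 0.5 means Cohen's d, attrition falls equally on both groups, and the parent is normal or at the minimum-efficiency bound. The route to 81% is unknown. Both routes that keep the 30:70 split differ from the description, one by leaving attrition in and the other by leaving out the Wilcoxon efficiency loss.

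The practical consequence is small. With normal data the detectable effect moves only from 0.50 to 0.51, and the 30% persistence used is more cautious than the study's own 38%, which would put normal-data power above the printed figure. The study's design and size are not called into question.

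**What to change.** Keep 180 patients and restate the sentence in one of these ways:

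- *Power 79% for effect size 0.5 (46 v 107 after 15% attrition, normal data; 74% at minimum asymptotic relative efficiency).*
- *Effect size 0.51 detectable with 80% power (46 v 107 after 15% attrition, normal data).*

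If 81% is the pre-attrition value at minimum efficiency, say so and give 74% as the value after attrition. If another parent distribution was assumed, name it. Say also that the effect size is a standardised mean difference, if that is what is meant. If the authors prefer the feasibility rate, 58 v 95 with 83% power (normal data) is the consistent replacement.

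The cost is one sentence. No patients are added and no analysis changes; the stated power becomes slightly less favourable unless the feasibility rate is adopted.

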## Ethics and dissemination

The FORECAST study has received ethical approval (South Central Oxford C, 18/SC/0263). All participants will provide informed written or electronic consent before participating in the study.

The dissemination strategy will be strongly guided by our PPIE activities (see below). This will be based on coproductions between patient partners and academics and will involve publication of findings in scientific journals, presentations at conferences, media pieces (mainstream and social media) as well as communication through charity partners.

Data will be made publicly available on the ALLEVIATE data hub (https://alleviate.ac.uk) and remaining bio-samples will be on-boarded to the Imperial Biobank. The data and samples will continue to be linked and will be available for future studies.

## PPIE and dissemination of findings

The FORECAST team consists of equal partners including patient partners, clinicians and researchers. Our aims have been shaped by the needs of people living with sciatica to ensure we address unmet needs. The PPIE plans will be shaped by the following members of FORECAST: (1) inclusion of two patient partners as coinvestigators (CR and CP). They will contribute as equal partners on the investigator team; (2) PPIE lead with extensive experience in involving patients’ voices in research ([name]); (3) diverse PAG consisting of six individuals with a lived experience of sciatica. Our patient partners and PAG provided early input to the original grant application and identification of key research activities within the project, particularly around including the feasibility work (eg, acceptability of testing and study procedures), study design (eg, selection of primary outcome measure) and strongly informed the writing of our funding application (eg, lay summary).

We will continue to work closely with people with lived experience of sciatica as we undertake this study, and our PPIE strategy will continue to be implemented throughout the lifetime of FORECAST. We will seek the perspective and guidance of our patient partners and PAG members on matters including, but not limited to participant recruitment and retention; barriers/facilitators of participation among seldom heard populations; data analysis and sensemaking of findings, organisation and coproduction of workshops, dissemination materials and public engagement activities. This will ensure that the patient perspective has been considered at all stages throughout the project.

We will also work closely with our patient partners and advisors on engagement and dissemination activities. This may include, but is not limited to, coproducing newsletters, lay summaries, website content, infographics, animated videos, and podcasts, as well as engagement activities to bring the project into a public sphere. We plan to work closely with the PAINSTORM research team and patient partners as well as other national and international pain and sciatica groups to promote the study and its subsequent findings. This would allow us to reflect on the way the conclusions are presented and identify any gaps which might lead to further research in the topic area. We also plan to hold conversations with our patient partners and PAG regarding planning and undertaking academic dissemination activities (eg, engagement with policy stakeholders, conference abstracts/presentations, manuscript preparation/publication). All individuals who contribute to this PPI advisory group will receive payment in accordance with current INVOLVE guidelines.
